Calcium gluconate (10 mL = 2.2 mmol [40 mg/dL]) and nebulised salbutamol (10 mg) will be administered to all participants, either before or after randomisation. While calcium is generally only recommended for patients with severe hyperkalaemia or those with ECG changes, a decision to include it for all randomised participants was made to prioritize participant safety in the ED setting. Up to 50% of patients with hyperkalaemia do not exhibit ECG changes [1,22]. Additionally, ECG interpretation often requires access to baseline ECG recordings which may not be available or accessible in the ED setting. The potential benefits of early cardiac stabilisation with calcium gluconate outweigh the risks associated with administration in patients without ECG changes, particularly in the context of a clinical trial. Adverse events related to its use have been shown to be very rare [8]. Additional therapies such as repeat calcium doses, potassium binders, or sodium bicarbonate may be used at the treating clinician’s discretion. All medications are administered *via* peripheral intravenous access. Clinicians should exercise appropriate care, as both hypertonic glucose and calcium gluconate carry a risk of thrombophlebitis and extravasation when administered peripherally. These adverse events are prospectively captured as secondary safety outcomes.

Throughout the six-hour intervention period, clinical reassessment will occur at regular intervals in accordance with routine ED practice and the study monitoring schedule. If potassium levels are unchanged or have increased at two hours post-study intervention, then the treating clinician may administer “rescue” insulin. Rescue insulin will also be given at any time in the event of clinical deterioration (e.g. worsening ECG changes or haemodynamic instability). Administration of rescue insulin does not preclude or delay escalation to renal replacement therapy, which remains at the treating team’s discretion and follows standard institutional protocols. Both rescue insulin administration and dialysis commencement are recorded as study events. Senior ED medical staff may unblind participants to manage clinical deterioration. Additionally, inpatient medical teams may request unblinding after the six-hour study period if the information is necessary for ongoing care.

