### Outcomes

The primary safety outcome is the incidence of hypoglycaemia (blood glucose <3.9 mmol/L (70 mg/dL), within 6 h post-treatment). Blood glucose is measured using validated bedside point-of-care glucometers. The primary non-inferiority outcome is the mean change in serum potassium (mmol/L) from baseline to 2 h post-treatment. Note that if a patient is enrolled based on a blood gas result due to clinical urgency, only the contemporaneous serum sample will be used for analysis. Secondary outcomes are severity of hypoglycaemia (ADA criteria); incidence of infusion-related complications including thrombophlebitis and extravasation; proportion of participants requiring rescue insulin therapy within 6 h post-treatment; mean change in serum potassium from baseline at 1 h and 4–6 h post-treatment; proportion of participants achieving a clinically significant potassium reduction (≥0.5 mmol/L [9 mg/dL] within 2 h); presence and resolution of hyperkalaemic ECG changes; serum insulin and C-peptide concentrations at baseline, 1 h, and 2 h post-treatment.

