## Statistical considerations

The target sample size for this study is 95 enrolments (approximately 48 per treatment arm). This sample size was primarily determined to provide 80% power to detect a statistically significant difference in the incidence of hypoglycaemia, assuming an incidence of 17% in the IDT group and 0% in the glucose-only group, using a two-sided significance level (α) of 0.05.

To account for repeat enrolments (maximum of two per participant), a design effect of 1.1 was applied. This was derived from an assumed intra-class correlation coefficient (ICC) of 0.3 and an average of 1.2 enrolments per participant. The ICC was conservatively selected to reflect potential within-subject correlation in hypoglycaemia risk. The final figure of 95 enrolments includes a 10% buffer to account for attrition or missing data (e.g. missed blood glucose measurements or haemolysed potassium samples).

This sample size also provides sufficient power for the primary non-inferiority objective serum potassium reduction at two hours. With a non-inferiority margin of −0.5 mmol/L (–9 mg/dL), an assumed true mean difference of 0.0 mmol/L and a standard deviation of 0.8 mmol/L (14.4 mg/dL), a minimum of 82 enrolments is required to achieve 80% power (α = 0.025, one-sided). Thus, the planned recruitment of 95 enrolments ensures the study is adequately powered for both primary endpoints.

All analyses will adhere to a modified intention-to-treat (mITT) principle, including participants who are randomised, receive the assigned intervention, and have at least one post-baseline potassium and BGL measurement. For participants commencing dialysis within the 6-hour observation period, data up to the point of dialysis initiation will be included. Per-protocol analyses will be undertaken as sensitivity analyses to assess potential bias arising from treatment cross-over (patients in the glucose only group receiving insulin).

For the primary safety outcome (hypoglycaemia incidence), proportions will be summarised by treatment group, and the between-group difference will be reported with 95% confidence intervals (CI). Groups will be compared using Fisher’s exact test. If clustering due to repeat enrolments is evident, a generalised linear model with a binomial error structure and robust standard errors adjusted for clustering will be used.

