For the primary efficacy outcome (change in serum potassium at two hours), mean (SD) reductions in each group and the between-group mean difference (95% CI) will be reported. Non-inferiority will be concluded if the lower bound of the 95% CI is greater than −0.5 mmol/L (–9 mg/dL).

Secondary outcomes will be summarised descriptively by treatment group. To compare groups, general linear models will be calculated with an identity or binomial error structure for continuous or categorical outcomes. Group differences will be reported as mean differences (continuous) and risk differences or risk ratios (categorical) with 95% CIs. Repeated measures data will be analysed using linear mixed-effects models, which account for within-subject correlation and accommodate missing data.

Missing data will be managed based on the extent of data loss. If missingness is minimal (<5%), cases with missing data will be excluded from analysis. Potassium results from haemolysed samples will be counted as missing data. Mixed-effects modelling will allow the inclusion of all available data, mitigating bias related to incomplete measurements.

No adjustment for baseline covariates is planned, as randomisation is expected to achieve balance between treatment groups. A two-sided p-value of <0.05 will be considered statistically significant. All analyses will be performed using an appropriate statistical software package.

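### Rescue insulin or dialysis before the 2 h potassium sample is handled so that, if it is commoner among poor responders on glucose-only, the primary analysis and its per-protocol check both lean towards non-inferiority

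*Protocol article*

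**What the plan says.** The Outcomes section defines the endpoint: "The primary non-inferiority outcome is the mean change in serum potassium (mmol/L) from baseline to 2 h post-treatment".

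The Intervention section has two triggers for rescue insulin. One acts on the 2 h potassium result, so it follows the primary sample. The other does not wait for it: "Rescue insulin will also be given at any time in the event of clinical deterioration (e.g. worsening ECG changes or haemodynamic instability"). The same section leaves dialysis to the treating team and records both rescue insulin and dialysis as study events.

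Statistical considerations then sets four rules that bear on these participants:

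- The analysis set is modified intention-to-treat and needs at least one post-baseline potassium and glucose value, not the 2 h potassium as such.
- On dialysis: "For participants commencing dialysis within the 6-hour observation period, data up to the point of dialysis initiation will be included".
- A per-protocol sensitivity analysis addresses glucose-only participants who received insulin.
- On missing data: "If missingness is minimal (<5%), cases with missing data will be excluded from analysis". Mixed-effects models are named for repeated measures and for using all available data.

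**The concern.** Two invented glucose-only records show how the rules work.

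- **Record A:** potassium 6.8 mmol/L at baseline and 6.9 at 1 h with a worsening ECG, insulin at 70 min, 6.0 at 2 h. As observed, this scores a reduction of 6.8 − 6.0 = 0.8 and counts as a responder at ≥0.5 mmol/L. The per-protocol analysis removes it.
- **Record B:** 6.8 at baseline, 6.9 at 1 h, dialysis at 90 min. The 2 h value is missing. The participant is excluded if missingness is below 5%, and otherwise enters only through a mixed model that assumes missing at random.

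In both, potassium had risen by 0.1 on glucose alone before escalation, and no stated analysis of the primary counts that against glucose-only. In a non-inferiority comparison, crediting the test arm with the comparator's drug and losing test-arm non-responders both pull the arms together. Agreement between the primary and per-protocol analyses would then reassure wrongly, because both can lean the same way.

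**Working it through.** **1. The plan's own figure.** Inputs from Statistical considerations: "With a non-inferiority margin of −0.5 mmol/L (–9 mg/dL), an assumed true mean difference of 0.0 mmol/L"; "a standard deviation of 0.8 mmol/L (14.4 mg/dL"); "a minimum of 82 enrolments is required to achieve 80% power (α = 0.025, one-sided").

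n per arm = 2 × (1.960 + 0.842)² × 0.8² / 0.5² = 40.2, rounded up to 41, so 82 in total. The stated figure reproduces and is not in dispute.

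**2. Precision.** The target is given as: "The target sample size for this study is 95 enrolments (approximately 48 per treatment arm"). Less the 10% buffer, 95 × 0.9 = 85.5, about 43 per arm. SE of the difference = 0.8 × √(2/43) = 0.173 mmol/L.

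**3. Assumptions, since the document gives no early-escalation rate.**

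- A share r of glucose-only participants (5% or 10%) and none on IDT are escalated before 2 h.
- Escalation falls on poor responders (correlation 0.7 with the reduction).
- Insulin adds 0.5 to 0.83 mmol/L to the observed 2 h reduction. The upper value is the whole IDT reduction in the small crossover trial cited in the Introduction, so it is generous for insulin given partway through the window.
- The true difference is exactly −0.5, so a correct analysis declares non-inferiority 2.5% of the time.

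**4. Formulas.**

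- 2 h value used as observed: shift = r × insulin gain.
- Participant removed (per-protocol, or excluded after dialysis): shift = 0.7 × 0.8 × φ(z_r)/(1 − r), where z_r is the normal quantile cutting off r and φ the normal density. At 5%: 0.56 × 0.103/0.95 = 0.061. At 10%: 0.56 × 0.175/0.90 = 0.109.
- False non-inferiority rate ≈ P(Z > 1.96 − shift/0.173).

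| Escalated, glucose-only vs IDT | Handling | Shift (mmol/L) | Rate by formula | Rate by simulation |
|---|---|---|---|---|
| 5% vs 0% | used, gain 0.5 | 0.025 | 3.5% | 3.4–3.6% |
| 5% vs 0% | used, gain 0.83 | 0.042 | 4.3% | 4.2–4.7% |
| 5% vs 0% | removed | 0.061 | 5.4% | 5.1–5.5% |
| 10% vs 0% | used, gain 0.5 | 0.050 | 4.7% | 4.6% |
| 10% vs 0% | used, gain 0.83 | 0.083 | 7.0% | 7.0–7.3% |
| 10% vs 0% | removed | 0.109 | 9.2% | 8.8–9.1% |

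Ranges in the last column are spread over separate simulation runs. In every row pair, removal is more biased than use as observed, so the per-protocol check is weaker than the analysis it is meant to test.

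**5. Escalation in both arms.** At 10% vs 2% the simulated rate is 4.1–6.0% with values used and 7.0% with such participants removed from both arms. At 10% vs 10% it is about 2.5% either way. That cancellation needs the same handling in both arms; a per-protocol removal confined to glucose-only, as the plan describes it, would not have it.

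**6. Failure scoring.** If early-escalated participants are scored at the smaller of zero and their pre-escalation reduction, the simulated rate at 5–10% vs 0% returns to about 2.5%.

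**The case against.** The strongest reply has five parts.

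**This is a condensed article, and detailed handling of such events belongs in the SAP.** True of what the article leaves out. But it does fix modified intention-to-treat, the cut at dialysis, the exclusion rule and the per-protocol check, and the point is what those stated rules do together.

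**Using values after rescue is a recognised treatment-policy approach.** It is, and under that target the as-observed result is not biased. The rates above are false only for the effect of glucose alone. The document, however, presents the treatment as a way of avoiding exogenous insulin, and a mean that includes rescue insulin does not answer that question by itself.

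**A reader might infer that there is no rule for rescue insulin and that early-dialysed participants are simply dropped.** The document does not support this. The per-protocol analysis addresses insulin in the glucose-only arm. A participant with a 1 h potassium stays in the analysis set. The exclusion clause applies only below 5% missing: 10% of one arm is 4.3 of 86, already 5.0% overall. A mixed model could keep the 1 h value, though under missing at random, and it does nothing for a post-insulin value that is observed.

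**A reader might infer that the bias certainly favours non-inferiority.** That is not supported either. Both arms can be escalated, and only an excess on glucose-only produces the as-observed bias. Such an excess is plausible: the cited crossover trial found reductions of 0.5 on glucose-only against 0.83 on IDT, potassium and ECG are taken at 1 h, and the limitations section concedes that glucose trajectories may unblind clinicians. It is not shown.

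**Early events may be few and need not mean non-response.** This stands. Unstable patients are excluded, all participants receive calcium and salbutamol, the potassium-based trigger follows the 2 h sample, and dialysis is discretionary. Five per cent of 43 is about two people. Rescue insulin within 6 h is also a secondary outcome, so these events are reported, though not within the primary.

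**Conclusion.** The concern holds in conditional form. No stated analysis of the 2 h potassium primary counts early escalation against glucose-only, and the one check aimed at insulin cross-over removes such participants. If escalation before 2 h is commoner on glucose-only and falls on poor responders, primary and sensitivity analyses lean the same way. At 5–10% versus 0% the shift is about 0.03–0.11 mmol/L against a 0.5 margin, and the false non-inferiority rate about 3.4–9% instead of 2.5%.

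The event rates, the correlation of 0.7 and the insulin gain are assumptions, and at equal rates the as-observed bias vanishes. The sample size of 82 is unaffected. This is worth correcting because the repair is cheap, not because the bias is certain or large.

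**What to change.** In Statistical considerations, pre-specify a sensitivity analysis of the 2 h primary, applied in both arms. A participant given rescue insulin or started on dialysis before the 2 h sample is analysed with the last potassium before escalation or with zero reduction, whichever is the smaller reduction. Records A and B would then each score a rise of 0.1 mmol/L.

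For the ≥0.5 mmol/L responder outcome, count only reductions reached before escalation. A participant already 0.7 lower at 1 h who starts dialysis at 90 min remains a responder, as the Outcomes definition implies.

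Report the number escalated before 2 h by arm. State that a non-inferiority conclusion will be interpreted cautiously if it does not hold in this analysis, and that the per-protocol analysis alone will not be relied on for this bias.

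The change is to analysis wording; treatment, rescue criteria and sample size stay as they are. The costs are a slightly less favourable estimate for glucose-only if early escalation occurs, and the need to capture the times of rescue insulin and dialysis, since the Intervention section says only that the events are recorded.

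### The per-protocol check targets glucose-only patients given insulin, but one trigger for that insulin is the 2 h potassium itself, so the check leans towards non-inferiority and cannot corroborate the mITT result

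*Protocol article*

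**What the plan says.** All references are to the protocol article.

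- **Analysis set** (Statistical considerations): "All analyses will adhere to a modified intention-to-treat (mITT) principle". The set requires randomisation, receipt of the assigned intervention, and at least one post-baseline potassium and glucose value. Rescue insulin is not a reason for exclusion.
- **Per-protocol** (same section): "Per-protocol analyses will be undertaken as sensitivity analyses", with the stated aim to "assess potential bias arising from treatment cross-over (patients in the glucose only group receiving insulin"). Only the glucose-only arm is named. The rule for leaving the set is not written out, and nothing is said about IDT patients who receive rescue insulin.
- **Rescue insulin** (Intervention): "If potassium levels are unchanged or have increased at two hours post-study intervention, then the treating clinician may administer" insulin. There is a second trigger: "Rescue insulin will also be given at any time in the event of clinical deterioration". Neither trigger is limited to one arm.
- **Endpoint** (Outcomes): "The primary non-inferiority outcome is the mean change in serum potassium (mmol/L) from baseline to 2 h post-treatment".
- **Decision rule** (Statistical considerations): non-inferiority is concluded when the lower 95% confidence bound lies above −0.5 mmol/L. The rule gives the per-protocol set no role.

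**The concern.** The first rescue trigger is a threshold on the primary endpoint: no fall in potassium at 2 h. If receipt of insulin takes a glucose-only patient out of the per-protocol set, patients leave because their endpoint was poor. The named cross-over covers one arm, so IDT patients with an equally poor 2 h value stay.

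The exclusion also has nothing to repair at 2 h. Insulin given because of the 2 h result comes after the sample that defines the endpoint and cannot have altered it. The protocol permits that treatment, so it is not a departure either.

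Readers of a non-inferiority trial commonly take agreement between the mITT and per-protocol results as reassurance. Here agreement would be partly built in, and most strongly when the mITT result is borderline or unfavourable. The same exclusion applied to hypoglycaemia over 6 h would take insulin-exposed patients out of the glucose-only count, again in favour of glucose-only therapy.

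**Working it through.** **1. The plan's own figure.** Inputs from Statistical considerations: margin 0.5, SD 0.8, true difference 0, one-sided α 0.025, power 80%. Per arm, n = 2(1.960 + 0.842)² × 0.8² / 0.5² = 2 × 7.85 × 0.64 / 0.25 ≈ 40.2, rounded up to 41, so 82 in total. This matches the stated 82.

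**2. How far the exclusion moves the arm mean.** Let the 2 h reduction be normal with mean μ and SD σ. The share with no fall is Φ(−μ/σ). The mean of those left, if all of that share are removed, is μ + σ·φ(μ/σ)/Φ(μ/σ).

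- μ = 0.50 (glucose-only arm of the small cross-over trial cited in the Introduction), σ = 0.8: 26.6% have no fall, and the mean rises from 0.50 to 0.86. The shift of 0.36 is 72% of the margin (0.36/0.5).
- μ = 0.33 (0.5 below the cited IDT mean of 0.83), σ = 0.8: 34% have no fall, and the mean rises to about 0.77. The difference from IDT moves from −0.50 to about −0.06.

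**3. Effect on the decision.** Simulation: 20,000 trials per setting, 48 IDT and 47 glucose-only enrolments (the planned 95), normal reductions, pooled-t 95% interval, margin −0.5. The true glucose-only mean is set 0.5 below IDT, so every declaration of non-inferiority is false. Glucose-only patients with no fall at 2 h are removed if rescued. Repeat enrolments, attrition and the deterioration trigger are left out.

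Percentage of per-protocol analyses declaring non-inferiority:

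| IDT mean reduction (assumed) | SD | All non-responders rescued | Half rescued |
|---|---|---|---|
| 0.83 | 0.8 | 78.5 | 18.3 |
| 0.83 | 0.6 | 67.7 | 15.5 |
| 0.83 | 0.4 | 42.9 | 11.4 |
| 1.0 | 0.8 | 60.5 | 14.3 |
| 1.0 | 0.6 | 41.7 | 11.3 |
| 1.0 | 0.4 | 16.5 | 6.6 |
| 1.2 | 0.8 | 38.3 | 10.8 |
| 1.2 | 0.6 | 20.2 | 7.5 |
| 1.2 | 0.4 | 6.2 | 3.9 |

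The mITT rate in the same settings is about 2.5% throughout. The SD of 0.8 is the protocol's; 0.83 is from the cited trial; the other means and SDs and the rescue uptake are assumptions, because the protocol gives none.

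**4. At the cited trial's means** (0.83 against 0.50, SD 0.8), non-inferiority is declared in about 17% of mITT analyses. In the one-arm per-protocol set it is 92% if all non-responders are rescued and 49% if half are.

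**5. Symmetry alone is not enough.** With an IDT mean of 0.83 and SD 0.8, excluding rescued non-responders from both arms still gives 34.0% (all rescued) or 6.7% (half rescued). The weaker arm loses more patients. The trigger must be removed from the definition, not merely applied to both arms.

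**The case against.** **The conclusion does not depend on this analysis.** A reader might infer that the trial would declare non-inferiority falsely, up to about 79% of the time. The documents do not support that. All analyses follow mITT, per-protocol is labelled a sensitivity analysis, and the decision rule does not mention it. The simulated error of the mITT test stays at about 2.5%. This objection stands in full.

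**The exclusion is implied.** The article gives a purpose and a parenthesis, not a list of exclusions. A fuller definition may sit in an analysis plan that is not shown. This stands as a caution. It does not remove the point, because the article does state which patients the analysis is aimed at, and that choice is the problem.

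**The clause has a legitimate use.** Insulin given before 2 h for deterioration can lower the 2 h potassium in the glucose-only arm and so flatter that arm in mITT. Checking for this is sound. Likewise, insulin in the glucose-only arm can cause hypoglycaemia that is then counted against glucose-only therapy. Both are fair questions, but the clause does not separate insulin given before the 2 h sample from insulin given because of it.

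**The large figures need strong assumptions.** Rescue after a poor 2 h value is discretionary, so removal of every non-responder is an upper bound. This trial also adds salbutamol in both arms and a glucose infusion, which may raise the mean response and leave fewer non-responders. This stands: at the mild end of the grid the rate is 3.9%, little above 2.5%.

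**Conclusion.** The point holds for the per-protocol check and not for the primary test. Read as written, the check selects on the primary endpoint, in the experimental arm only. For patients rescued because of the 2 h result, the direction is fixed: it favours non-inferiority. It cannot serve as independent support for the mITT finding.

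The size is uncertain: about 4% to 79% of per-protocol analyses at the margin, against 2.5% in mITT, over the assumed means, SDs and rescue uptake shown. The result also rests on normal reductions and on the inference that insulin receipt leads to exclusion. It should be corrected before analysis, but it is not evidence that the trial's main conclusion is invalid.

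**What to change.** These changes concern the analysis only and leave the rescue rules as they are.

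1. For the 2 h potassium endpoint, define the per-protocol set by departures that occur before the 2 h sample and are not triggered by the outcome, such as a wrong or incomplete study bag or an entry violation. Apply the definition identically in both arms.
2. State that rescue insulin given after the 2 h sample never excludes a participant from that analysis.
3. For insulin given before the 2 h sample, keep the participant and prespecify the handling in both arms. One option is the last potassium before rescue, with an unfavourable value as a sensitivity analysis; other strategies are acceptable if fixed in advance.
4. For 6 h hypoglycaemia, do not present a set without insulin-treated glucose-only patients as confirming the mITT safety result.

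The cost is a few sentences and a small extra analysis. It needs the time of rescue insulin. The article says that administration is recorded as a study event but does not mention its timing, so the timing should be captured with that record. Recruitment is planned to November 2027, which leaves room to do this before analysis.

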### Intervention

Participants will be allocated *via* stratified (potassium <6.5 mmol/L [117 mg/dL] or ≥6.5 mmol/L [117 mg/dL), block randomisation to receive either glucose-only therapy or insulin–dextrose therapy (IDT) in a 1:1 ratio with the use of sequential, opaque, sealed envelopes. Envelopes are opened by members of the research team or clinical pharmacists only after formal participant enrolment is confirmed and documented. Interventions will be prepared by the same staff who open the envelope and away from clinical areas. Study solutions will appear visually identical to ensure blinding of participants and treating clinicians. The study period extends for six hours following randomisation. In eligible participants, treatment commences as soon as possible after enrolment.

In the glucose-only arm, participants will receive 100 mL of 50% dextrose administered over 10 min, followed immediately by 250 mL of 10% dextrose infused over two hours.

In the insulin–dextrose arm, participants will receive 10 units of intravenous insulin (Actrapid) mixed with 50 mL of 50% dextrose and 50 mL of 0.9% sodium chloride (total 100 mL), administered over 10 min, followed by 250 mL of 0.9% sodium chloride infused over two hours.

Infusion bag 1 (100 mL) will be prepared by modifying 0.9% sodium chloride bags according to the assigned intervention. Study labels will be affixed to the front of each bag. Infusion bag 2 (250 mL) will consist of the proprietary product used in each arm without alteration; these bags will be concealed using an opaque black sleeve to mask product identity, with study labels applied to the exterior.

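### The 95 enrolments do not follow from the planned Fisher's exact test; after the plan's own allowances its power for hypoglycaemia is about 75–78% rather than 80%, and Boschloo's test would recover this without more patients

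*Protocol article*

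**What the plan says.** All of this is in the Protocol article, Statistical considerations, unless noted.

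- **Sample size.** "This sample size was primarily determined to provide 80% power to detect a statistically significant difference in the incidence of hypoglycaemia". The planning rates are 17% with insulin–dextrose and none with glucose-only, at a two-sided 5% level. The target is 95 enrolments, about 48 per arm. It includes a design effect of 1.1 for repeat enrolments (ICC 0.3, 1.2 enrolments per participant on average) and a 10% buffer for attrition or missing data. No sample-size formula is named.
- **Test.** "Groups will be compared using Fisher’s exact test". If clustering from repeat enrolments is evident, a binomial generalised linear model with cluster-robust standard errors is used instead.
- **Estimate.** The difference in proportions is to be reported with a 95% confidence interval, whose method is not named.
- **Allocation** (Intervention section). Enrolments are allocated "in a 1:1 ratio with the use of sequential, opaque, sealed envelopes".

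**The concern.** A power statement belongs to a particular test. The article fixes both the power and the test, so they should agree. Fisher's test conditions on the total number of events, and with few events it is conservative: its attainable significance levels are coarse and often well below 5%. A size taken from a normal approximation will then fall short when Fisher's test is applied.

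Hypoglycaemia is the outcome that primarily set the sample size. The section on feasibility says the target is close to the number of eligible presentations expected over two years, so there is little room to recruit out of a shortfall. A secondary worry is that, near the decision boundary, the two-sided Fisher result depends on which arm happens to be one patient larger.

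**Working it through.** **Inputs.** Incidences 0.17 and 0.00, two-sided alpha 0.05, power 80%, design effect 1.1 and buffer 10% (Statistical considerations); 1:1 allocation (Intervention).

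**1. Reproducing 95.** Unpooled normal approximation:

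n per arm = (1.96 + 0.8416)² × [0.17 × 0.83 + 0] / 0.17² = 7.849 × 0.1411 / 0.0289 = 38.3, so 39 per arm and 78 in total.

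78 × 1.1 × 1.1 = 94.4, rounded up to 95 (dividing by 0.9 for the buffer gives 95.3).

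Other formulas, with the stated 1.1 design effect:

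| Formula | Per arm | Enrolments |
|---|---|---|
| Unpooled normal | 39 | 95 |
| Pooled normal | 42 | 102–103 |
| Continuity-corrected | 53 | 128–130 |
| Arcsine | 22 | 53 |
| Fisher, exact | 46 | 111–112 |

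Fisher line: 92 × 1.1 × 1.1 = 111.3, or 92 × 1.1 / 0.9 = 112.4. The ICC and mean enrolments imply a design effect of 1 + 0.2 × 0.3 = 1.06. With 1.06 the pooled formula comes near (about 96–99), but Fisher still gives about 107–108.

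**2. What Fisher needs.** With no glucose-only events, power = P(X ≥ c), where X ~ Binomial(n in the insulin–dextrose arm, 0.17) and c is the smallest count significant against 0. With equal arms, 5 versus 0 gives p = 0.0545 at 39 per arm and 0.0553 at 43 per arm, so c = 6. P(X ≥ 6) is 67.1% at 39, 76.2% at 43, 79.99% at 45 and 81.7% at 46.

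The 39 and 43 come from the plan's allowances: 95 × 0.9 = 85.5 (about 43 per arm), and 85.5 / 1.1 = 77.7 (about 39 per arm).

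**3. The one-patient flip.** Take 85 analysed and 5 events, all in one arm.

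- All 5 in the arm of 43: C(43,5)/C(85,5) = 962,598 / 32,801,517 = 0.0293.
- All 5 in the arm of 42: C(42,5)/C(85,5) = 850,668 / 32,801,517 = 0.0259.

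The usual two-sided Fisher p adds every table no more probable than the one observed. If insulin–dextrose is the arm of 43, the opposite table counts: p = 0.0293 + 0.0259 = 0.055, not significant. If it is the arm of 42, the opposite table is more probable and is left out: p = 0.026, significant. Power moves from 76.2% (43 insulin–dextrose, 42 glucose-only) to 86.4% (42 and 43).

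**4. Averaging over arm sizes.** Each of the 47 or 48 enrolments per arm is retained independently with the stated probability. The design effect is treated as a further reduction in sample size.

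| Analysed | Fisher, equal arms | Fisher, average | Boschloo, equal arms | Boschloo, average |
|---|---|---|---|---|
| All 95 | 85% (48/47) or 92% (47/48) | – | 93% (48/47) or 92% (47/48) | – |
| 10% loss | 76% | 81–84% | 88% | 86–87% |
| 10% loss and 1.06 | – | 78–80% | – | 82–83% |
| 10% loss and 1.1 | 67% | 75–78% | 82% | 80–81% |

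The all-95 row gives the two nearest splits, insulin–dextrose arm first. If Fisher's two-sided p is defined by doubling the one-sided p, its averages are lower: 79–80% with 10% loss and 71–73% with the 1.1 design effect added.

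**5. Boschloo's test.** Here the two-sided p is twice the smaller one-sided p. At 5 versus 0 (insulin–dextrose arm first) it is 0.031 (39/39), 0.032 (42/43), 0.038 (43/42), 0.040 (43/43) and 0.040 (47/48 and 48/47). It rejects on both sides of the flip. P(X ≥ 5) is 81.6% at 39 and 87.7% at 43, with maximum size 0.0495.

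The definition matters. If tables are ordered by the two-sided Fisher p instead, 43/42 gives p = 0.0503 and 42/43 gives 0.021, so the flip remains.

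**The case against.** **A reader might infer that the trial has only 67–76% power and would miss its safety outcome one time in three.** The documents do not support that. Those figures need exactly equal arms, or an insulin–dextrose arm that is slightly larger. An odd total of 95 cannot split equally, and losses make equality unlikely later. With 10% loss alone the average is 81–84%, so the stated 80% is met; with no loss it is 85–92%. The 67% figure also takes off the design effect and then applies Fisher's test, whereas the plan moves to a clustered model if clustering is evident. It further uses the rounded 1.1 rather than 1.06.

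**The formula is inferred.** The article names none. What stands without inference is that Fisher's test, with equal arms and the plan's own inflations, does not lead to 95.

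**A reader might also infer that the test and the confidence interval must contradict each other at 5 versus 0.** Approximate intervals can exclude 0 while Fisher's p exceeds 0.05. But the interval method is not named, and an interval obtained by inverting an exact test need not do so. The outcome itself has a probability of about 8–15% under the planning assumptions (39 to 48 per arm), and the clash also needs an unfavourable split.

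**Fisher's test is valid.** It keeps type I error below 5%, so no false safety claim follows. The cost is power. Nor does Boschloo's test win for every split: at 37 insulin–dextrose and 41 glucose-only, the usual Fisher test already rejects at 4 versus 0 (p = 0.046), while the doubled Boschloo test needs 5. Its advantage is on average and in its stability.

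**Conclusion.** The concern holds in a limited form. The stated 80% power and the named test do not match: Fisher's test needs about 111–112 enrolments under the plan's own inflations, not 95. The shortfall is modest. It is about 2 to 5 percentage points on average when both of the plan's allowances are taken off (75–78%), 13 points with exactly equal arms (67%), and nil on average with attrition alone. The dependence of the 5-versus-0 result on a single patient is a separate weakness of the same choice.

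The figures assume the planned incidences of 17% and 0%, losses that are random and independent of arm, and a design effect that acts as a simple reduction in sample size. The loss is one of power; neither type I error nor the estimated difference is at fault.

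**What to change.** In Statistical considerations, before unblinding:

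1. Replace Fisher's test with Boschloo's unconditional exact test at two-sided 5%. State the two-sided definition; twice the smaller one-sided p is the one that removed the flip in the check above.
2. Name a confidence interval for the risk difference that is compatible with that test.
3. Restate the power for that test: about 82% at 39 per arm and 88% at 43 per arm (80–81% and 86–87% averaged over arm sizes). Name the formula behind 95.

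If Fisher's test is kept, restate its power as about 75–78% net of both inflations (67% with equal arms) and state its two-sided definition.

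The cost is a few sentences and a less familiar test, with no added patients or data. Like Fisher's, Boschloo's test treats enrolments as independent, so repeat enrolments still need the separate clustered analysis.
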